## Abstract

**Background:**

This paper describes the rationale, intervention development, study design and results from the pilot feasibility study of the Keep On Running (KOR) trial. KOR aims to test a web-based brief theory-based intervention, targeting maintenance of recreational running behavior over time (i.e. relapse preventing).

**Methods:**

Intervention development was based both on Self-Determination Theory and on Self-Regulation Theory. As part of it, a pilot study was implemented (*n*=18) to measure intervention adherence and participant satisfaction in order to establish the feasibility and acceptability of the intervention toolkit. Furthermore, this pilot study was also used to test the feasibility and acceptability of the questionnaires selected to be part of the later RCT.

**Results:**

Pilot intervention acceptability was good, but overall adherence was low. Features such as feedback and social sharing should be added to the toolkit. The main trial should lessen questionnaire length and include data from usual monitoring gadgets and apps (APIs). The protocol of the RCT was adjusted to test the efficacy of the refined final version of the intervention, and the RCT that will test it, contributing to the understanding of recreational running sustainability, allowing the optimization of future interventions aimed at physical activity promotion.

## Background

While benefits of regular physical activity (PA) and exercise are well established (Kraus et al., 2019; Oja et al., 2015), insufficient PA and the prevalence of sedentary behavior remain as challenges in health promotion (Ding et al., 2016; Guthold, Stevens, Riley, & Bull, 2018). Although research suggests that behavior change interventions can increase PA over the course of an intervention, these effects are generally not persistent after the intervention ends (McEwan, Rhodes, & Beauchamp, 2020).

Along with initial involvement, sustained adherence is a well-known challenge in exercise contexts, as many people struggle to keep up their behavior for longer than 6 months (Kahlert, 2015; Marcus et al., 2000). Research on the characterization of people who are physically active (Cortis et al., 2017; Sawyer, Ucci, Jones, Smith, & Fisher, 2017) and manage to sustain their PA behavior (Amireault, Godinb, & Vézina-Imb, 2013) is extensive. While most of the research about behavior sustainability report how many discontinue practice, only few studies addressed the psychological mechanisms of behavior maintenance (Kwasnicka, Dombrowski, White, & Sniehotta, 2016), such as the quality of their motivation, the emotions and gains they experience while exercising, or the regulatory resources they use to overcome exercise-related challenges and barriers.

Self-determination theory (SDT) (Deci & Ryan, 2000, 2008) can provide a valid framework to study PA maintenance. The underlying premise of SDT is that sustained motivation is elicited from within the person (not imposed by someone else) and that supporting clients’ basic needs for autonomy (need to feel a sense of choice, volition and self-endorsement), competence (need to feel a sense of mastery and capacity to accomplish the behavior), and relatedness (need to feel meaningfully connected to others, valued and understood) will best promote the initiation and maintenance of behavior change, by fostering autonomous motivation and well-being. Conversely, when these three needs are thwarted, people will tend to develop controlled motivations, regulating their behavior based on external contingencies and internalized self-judgments (Vansteenkiste & Ryan, 2013).

In addition, not all types of goals have the same consequences (Ryan, Sheldon, Kasser, & Deci, 1996). The outcomes that individuals are pursuing through the new behavior can have intrinsic or extrinsic qualities, which can also influence behavior maintenance. Relative to ‘extrinsic goals’ (e.g. wealth, social recognition, physical attractiveness), ‘intrinsic’ goals (e.g. health, personal growth, social connectedness) tend to be regulated by more self-determined forms of behavioral regulation and are thought to result in improved self-regulation and longer-term outcomes (Ingledew & Markland, 2009).

In summary, SDT interventions have a significant effect on health behavior change (Sheeran et al., 2020). Additionally, SDT-informed interventions positively affect indices of health, partly due to increases in internalization, self-determined motivation and support from social agents, and were stronger at the end of interventions than at follow up (Ntoumanis et al., 2020). The effect sizes seen in PA interventions are mediated by our current theories (Rhodes, Boudreau, Josefsson, & Ivarsson, 2020). Taken together, recent evidence suggests that SDT (Deci & Ryan, 2000) can provide a valid framework to study PA maintenance. Furthermore, aligning motivational and post-motivational (i.e. self-regulatory) features represents a promising avenue for lasting behavior change (Hagger & Chatzisarantis, 2014). In this regard, self-regultory skills such as self-monitoring, individualized goal setting or action planning, have been identified as important mediators of the effect of interventions on long-term physical activity and as potentially core features of effective behavior change/maintenance interventions (Rhodes et al., 2020).

Thousands of health-related applications (apps) are available world-wide for smartphones and represent a unique opportunity to reach a broad audience of users. The most popular apps are for exercise, diet, and weight management, and 500 million users use mobile health applications. Mobile health interventions have surged in popularity but their implementation varies widely, and evidence of effectiveness is mixed (Dugas, Gao, & Agarwal, 2020). When trying to understand design features through the SDT lens, only one-fourth of the sample provided users support for the three basic psychological needs of competence, autonomy and relatedness (Villalobos-Zúñiga, 2020). It was found that prompts and cues, techniques of personalization, feedback and monitoring, goal setting and action planning were most commonly used in effective mobile health interventions (Dugas et al., 2020).

### The case for recreational running

Running is one of the most popular forms of leisure-time exercise (Andersen, 2020; Running-USA, 2020; Teixeira, Marques, Lopes, Sardinha, & Mota, 2019) in part because it is inexpensive and can be performed anywhere, almost at any time. In addition, it requires little technical skills, is relatively safe, and it is easy to learn. The health benefits of running are vast, including prevention of obesity, hypertension, dyslipidemia, type 2 diabetes, osteoarthritis and hip replacement, benign prostatic hypertrophy, respiratory disease, cancer, disability, reduction of cardiovascular, and all-cause mortality (Lavie et al., 2015; Lee et al., 2014; Pedisic et al., 2019).

Running stimulates the interest of the research community, especially because of the long hours of training throughout the year and the large number of events runners participate in (Zach et al., 2017). This suggests that motivational aspects related with training for and completing a race may be unique (Zach et al., 2017). With this in mind, running clubs/groups may provide a novel testbed for understanding why people adopt recreational running and how motivational factors can support PA maintenance.

To better promote running sustainability and its long-term health benefits, it is crucial to understand individuals’ running experiences and outcomes, as well as the factors that predispose them to engage in this activity. Studying the antecedents and outcomes of running motivation, as well as the efficacy of different types of interventions to promote running behavior will enhance the understanding of the phenomenon, possibly creating new insights into the effective promotion of PA maintenance.

To our knowledge, no previous study has been designed to test the efficacy of interventions to promote sustained running behavior and identify the mechanisms behind it. Future interventions will aim to test if motivation and self-regulation mediators can be successfully modified via a digital-based intervention. This will ultimately lead to sustained adherence to an activity that participants have chosen and appear to enjoy, via large-reach interventions, capitalizing on the widespread availability of running clubs/events and increased reliance of exercisers on remote technologies.

This paper describes the rationale, intervention development, study design, and pilot study of the Keep On Running (KOR) trial. KOR aims to test a brief theory-based intervention, delivered through digital technology (web app), targeting maintenance of recreational running behavior over time (i.e. relapse prevention) after being voluntarily initiated in the previous 3 months. The pilot study was focused on intervention adherence and participant satisfaction in order to establish the feasibility and acceptability of the intervention toolkit. Furthermore, it was also used to test the feasibility and acceptability of the questionnaires selected to be part of the later RCT.

### Study objectives and hypotheses

The study's objective is to develop and present a new digital toolkit aiming at maintenance of recreational running behavior over time (i.e. relapse preventing), and evaluate whether it can be delivered and accepted by participants. We hypothesize that the built intervention can be delivered and will be accepted by the participants, and tested by the RCT.

## Methods

### Study design

KOR is a Randomized controlled trial (RCT). It was developed based on a logic model (Figure 1), adapting the motivational and self-regulation arm of the NoHoW study (Marques et al., 2020; Scott et al., 2019). The trial involved combinations of two conditions: (a) organized (i.e. Programa Nacional de Marcha e Corrida – PNMC) vs. free recreational runners (FRR), and (b) self-regulation and motivation (SRM) intervention vs. no intervention.

**Figure 1. F0001:**
[figure not shown]
KoR's Logic Model.

As a result, it comprises four different groups (Figure 2): (i) a group of runners enrolled in the running program and additionally receiving the theory-based intervention (PNMC + SRM); (ii) a group of runners merely participating in the organized running program (PNMC); (iii) a group of FRR receiving the theory-based intervention (FRR + SRM); and lastly, (iv) a group of FRR receiving only general information on running (i.e. control group).

**Figure 2. F0002:**
[figure not shown]
Organization of participant groups.

This approach was taken because (a) comparing runners belonging to PNMC with FRR (i.e. control group) allows examining the effect of the PNMC on behavior maintenance; (b) comparing FRR enrolled in the SRM intervention with FRR allows testing the effectiveness of a light-touch intervention on motivational and other psychological variables, and on behavior maintenance; and (c) comparing runners belonging to PNMC and receiving the SRM intervention with FRR receiving the SRM intervention will allows examining whether the SRM intervention has an additional effect on the study outcomes. Trial duration is one year with assessments at 6 weeks, and 6 and 12 months postbaseline (Figure 3).

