### Recruitment and randomization

Part of the runners will be recruited from the PNMC program, which consists in 2–3 supervised running group-sessions of 10–20 runners per week, lasting 90 min each. Certified trainers lead these sessions, apply specific methodologies for running and for walking sessions. Prior to their enrollment, trainers must complete a training course. The other set of runners (which run freely, on their own) will be recruited from the community (recreational runners). To recruit this sample, we will use online advertisement and running events list servers, reach out for running clubs, and partnerships with both state and private organizations.

We will use a rolling recruitment strategy: participants will join the study as soon as they are considered eligible to facilitate management of available human resources. Each set of runners will be randomly assigned to the KoR intervention group or the control group general information group in a 1:1 ratio, stratified by group (PNMC and FRR). The method of randomized permuted blocks will be used, with random block lengths (4 or 6) (Broglio, 2018). Because participants will know which arm of the study they are in, blinding is not possible.

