### Data collection

Participants will go through four assessment periods at baseline, 6 weeks (post-program), 6 months, and 12 months follow-up. The training and clarification session will be completed by telephone to ensure participants are equipped with the skills to access the intervention contents. Before the first, third and fourth assessment periods, eligibility will be checked against inclusion and exclusion criteria through a telephone screening/re-screening call, 1 week prior to each visit. Participant's timeline is shown in Figure 3.

*Assessment* 1 (baseline): Clarification session about the study. If participants are still interested in enrolling in the study, eligibility will be checked, and they will be asked to fill out an informed consent form. Randomization and allocation to one of the four arms of the trial will be performed. Data on demographics and potential psychological moderators will be collected. A battery of psychological and behavioral questionnaires will be completed online using google forms (in one-week time) – running behavior (i.e. frequency and minutes per week), motivations, basic psychological needs, motives and gains, self-regulation skills, passion, flow, and vitality. This task is estimated to take approximately 1 h, but participants will be able to do breaks and return later to complete the psychometric evaluation during that week. Debrief on how to use the KOR web-based intervention content – the toolkit (approximately 1 h).

*Assessment*s 2 and 3 (intervention's end and 6-month follow-up). Email reminder prior to this evaluation period will be sent. The same battery of psychological and behavioral questionnaires will be completed online using google forms (in one-week time) – running behavior (i.e. frequency and minutes per week), motivations, basic psychological needs, motives and gains, self-regulation skills, passion, flow, and vitality –, and will take approximately 1 h.

*Assessment* 4 (12-month follow-up). Running behavior maintenance will be assessed through a telephone call, asking participants whether they keep running at their initial level or higher, or not.

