### Analytical strategy

Statistical analysis will be performed using SPSS Statistics version 25.0 (SPSS Inc., an IBM Company, Chicago IL, USA). Descriptive statistics will be calculated (mean, standard deviation and range). Repeated measures with Bonferroni corrections for adjusted comparisons will be used to examine differences between each intervention group(PNMC or SRM) and controls (i.e. free recreational runners), at all assessment points, in the primary and secondary outcomes measured. Statistical significance will be set at *p* < 0.05.

Mediation analysis, will test the psychological mechanisms underlying changes in running behavior from baseline to post program, 6 and 12 months. Multilevel modeling will be used to determine the SRM intervention effect on these motivational variables, with intervention group (SRM vs. Control group) as the between-subject factor and change in self-regulation and competence for running at baseline, 6–8 weeks, 6months and 12 months, serving as dependent variables. If necessary, multiple imputation methods will be implemented to provide robust results for primary and main secondary outcomes.

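### PNMC membership is not randomised, yet the plan reads PNMC versus free runners as a programme effect and tests PNMC as an intervention

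*Protocol article*

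**What the plan says.** All references are to the protocol article.

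- **Study design** calls KOR a randomised controlled trial built from two crossed conditions, organised versus free running and SRM versus no intervention. This gives four groups: PNMC+SRM, PNMC alone, FRR+SRM and FRR control. Three contrasts are then justified. The first is that "comparing runners belonging to PNMC with FRR (i.e. control group) allows examining the effect of the PNMC on behavior maintenance". The second is FRR+SRM against FRR. The third is PNMC+SRM against FRR+SRM, meant to show whether SRM adds an effect.
- **Recruitment and randomization** states that "Part of the runners will be recruited from the PNMC program"; the free runners are recruited separately, from the community. On allocation it says: "Each set of runners will be randomly assigned to the KoR intervention group or the control group general information group in a 1:1 ratio". Whether a runner is PNMC or FRR enters this allocation only as the stratification factor.
- **Data collection**, Assessment 1, states: "Randomization and allocation to one of the four arms of the trial will be performed".
- **Analytical strategy** plans repeated-measures comparisons with Bonferroni correction to examine "differences between each intervention group(PNMC or SRM) and controls (i.e. free recreational runners), at all assessment points", on primary and secondary outcomes, with significance at p < 0.05.

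**The concern.** A stratification factor is something a participant brings to the trial; it is not assigned. Whether a runner belongs to PNMC was settled before enrolment, by the runner. The trial therefore randomises one factor (SRM), but the first Study design contrast and the Analytical strategy treat the other as an intervention whose effect can be read from a group difference.

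The outcome makes this matter. The trial studies whether people keep running. Someone who has joined a programme with two or three supervised 90-minute group sessions a week may differ from a solitary runner in motivation, available time and liking for company. Some of these are traits the trial itself measures as mediators or moderators.

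The baseline is also not clean for this contrast. PNMC runners are recruited from within the programme, so their baseline running may already contain some programme effect. At 12 months the question is whether they still run at their initial level, so that reference level may be affected too.

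At stake is a causal statement about a national programme, published under the label of a randomised trial, that the design cannot support.

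**Working it through.** **1. Which contrasts are randomised.** Setting the four groups in Study design against the allocation rule in Recruitment and randomization:

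| Contrast | What differs | Randomised? | Listed in Study design? |
|---|---|---|---|
| FRR+SRM vs FRR control | SRM | Yes | Yes (second) |
| PNMC+SRM vs PNMC | SRM | Yes | No |
| PNMC vs FRR control | Programme membership | No | Yes (first) |
| PNMC+SRM vs FRR+SRM | Programme membership | No | Yes (third) |

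Two of the three listed contrasts are not randomised, and one of the two randomised SRM contrasts is not listed. The third listed contrast cannot answer its own question: SRM is present on both sides and cancels. An additional SRM effect among PNMC runners needs PNMC+SRM against PNMC, or the SRM-by-stratum interaction.

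**2. What selection alone could do.** The plan gives no figure for this, so the following is an illustration.

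Inputs:
- n = 55 per group (Power calculations and sample size estimation; taken as stated, without relying on how it was derived).
- Two-sided alpha 0.05, critical value 1.96, before Bonferroni.
- True PNMC effect zero.
- Prognostic difference δ between PNMC and FRR runners, in SD units: assumed. The value 0.23 is chosen because it equals the effect size the plan expects for its primary outcome.

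Formula for an uncorrected comparison of two means: z = δ × √(n/2); rate of significant results = Φ(z − 1.96) + Φ(−z − 1.96).

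For δ = 0.23 and n = 55: √(55/2) = 5.244 and z = 0.23 × 5.244 = 1.206. The rate is Φ(−0.754) + Φ(−3.166) = 0.225 + 0.001 = 0.226, about 23%.

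| Assumed δ | 55 vs 55 |
|---|---|
| 0.10 | 8% |
| 0.20 | 18% |
| 0.23 | 23% |
| 0.30 | 35% |
| 0.50 | 75% |

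If the SRM and no-SRM groups were pooled within each set (110 vs 110), δ = 0.23 would give 40%. A larger sample makes the false finding more likely, because the problem is bias and not imprecision.

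**3. Bonferroni.** The number of comparisons is not given. With two (assumed), alpha is 0.025 and the critical value 2.241. At δ = 0.23 and 55 vs 55 the rate is Φ(1.206 − 2.241) = Φ(−1.035), about 15%, against a nominal 2.5%. The correction lowers the rate but leaves the bias in place.

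**The case against.** The strongest reply is that the allocation rule is stated plainly in Recruitment and randomization, and that a runner randomised within a stratum does end up in one of four arms. That stands. A reader might infer from Data collection that PNMC membership itself is randomised; the sentence is loose and should be reworded, but the recruitment section clarifies it.

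Other stronger readings are also not supported:

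- **That the comparison is unadjusted at 0.05.** The Analytical strategy specifies Bonferroni correction and does not describe the comparison as unadjusted. Baseline running enters a repeated-measures comparison. No covariates are named, but an article may leave those to an analysis plan. What remains is that including baseline running handles a difference in starting level, not a difference in how likely the two sets are to keep going.
- **That PNMC runners attended for up to three months before baseline.** The three-month limit is on running and applies to both sets. Prior programme attendance is a reasonable inference, but its length is not stated.
- **That clustering makes the p-value too small by a known amount.** The article mentions sessions of 10–20 runners led by certified trainers. It does not say that groups are stable or that each has one trainer, and it gives no intraclass correlation. With 1:1 randomisation, a group of at most 20 contributes about 10 to a single arm. At an assumed correlation of 0.05 that would give a type I error of 7.7% before Bonferroni; with 2–3 runners per group, 5.3–5.6%. None of these figures can be derived from the document.
- **That PNMC carries the same weight as SRM in the trial's aims.** The aim is to test the SRM toolkit, and the only trial hypothesis in the Discussion concerns SRM against control.

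None of this reaches the core. The recruitment section makes PNMC versus FRR non-randomised, while Study design and the Analytical strategy read it as an intervention effect.

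**Conclusion.** The point holds as a matter of text. PNMC versus FRR compares two self-selected populations, and neither Study design nor the Analytical strategy limits it to an observational reading. The same applies to PNMC+SRM versus FRR+SRM, which additionally cannot show what it is said to show.

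The direction and size of the bias are unknown. The 23% figure rests on an assumed prognostic difference of 0.23 SD, no true programme effect, 55 per group and an uncorrected two-sided 5% test. It shows that selection no larger than the effect the trial hopes to find could often produce a significant result; it does not estimate the actual bias.

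The SRM comparisons within each stratum are randomised and unaffected, so the central question of the trial is not damaged. The change should be made before results are reported, but it does not put the trial itself in doubt.

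**What to change.** 1. Reword the allocation sentence in Data collection to match the recruitment section: participants are randomised to SRM or general information within the PNMC or FRR stratum.
2. Name the within-stratum SRM contrast as the primary comparison.
3. Label PNMC versus FRR an observational secondary comparison. Adjust it for baseline data already planned (running minutes, age, gender, physical activity history, autonomous functioning, motivation) and report it as an association. Adjustment reduces confounding but does not remove it. If programme attendance began before baseline, adjusting for baseline running or motivation may also take out part of any programme effect; the report should say so.
4. Replace the third Study design contrast with PNMC+SRM versus PNMC, or with the SRM-by-stratum interaction.
5. Minor: if PNMC runners train in stable groups, record the group and use a partially nested model, with a random group effect on the PNMC side only, since free runners have no such group.

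The cost is wording, one extra recorded item where groups are stable, and a modest change to the model. No further participants or questionnaires are needed. The downside is a weaker claim for PNMC.

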## Discussion

This paper presents the rationale, development, study design, methods and pilot application of the KOR trial, aimed at testing the effect of the intervention on the maintenance of recreational running behavior over time, after being voluntarily initiated by community-dwelling adults in the previous 3 months. This ‘light-touch’ intervention is unique in that it approaches running behavior and its sustainability, delivered in a digital format, and based on strong theoretical foundations.

We hypothesize that the sustainability of running behaviors will be higher in the SRM groups compared to the control group. Change in running behavior (e.g. frequency and minutes of running per week) and secondary outcomes related to the quality of the running experience (e.g. passion, flow, vitality) will be used as the dependent variables.

Additionally, the results of the pilot feasibility study, intended at testing intervention adherence, participant satisfaction, and questionnaire acceptance, were also presented. Overall, the pilot study indicated that the intervention has good acceptability, feedback was very positive, but toolkit interaction decreased after the first weeks, which is common in web-based interventions (Baumel & Yom-Tov, 2018). Moreover, the generalized use of other running-related devices, applications and communities may have overlapped with the anticipated content of the toolkit, challenging participants’ interaction. The completion ratio of the post-program questionnaire was low, maybe due to its extension and burden, but also because its timeline ended near the summer break.

The main trial should reduce questionnaire length and burden, and include interface with usual monitoring gadgets and apps (APIs), to increase data detail and prevent ‘unnecessary’ data insertion by the participants. Features such as feedback and social sharing, added to the goal setting features already integrated in the toolkit, may also increase attractiveness (Hosseinpour & Terlutter, 2019).

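### The contrast said to show an additional effect of SRM compares two arms that both receive it, and the randomised PNMC+SRM vs PNMC comparison is never named

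*Protocol article*

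**What the plan says.** The Study design section of the protocol article describes four groups: PNMC+SRM, PNMC, FRR+SRM and FRR. It gives three comparisons:

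- (a) PNMC runners against FRR controls, meant to show what the organised programme does for maintenance.
- (b) SRM against no SRM among runners outside the programme: "comparing FRR enrolled in the SRM intervention with FRR allows testing the effectiveness of a light-touch intervention".
- (c) The comparison at issue here, "comparing runners belonging to PNMC and receiving the SRM intervention with FRR receiving the SRM intervention", for the purpose of "examining whether the SRM intervention has an additional effect on the study outcomes".

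Under Recruitment and randomization, PNMC runners come from an existing programme and FRR runners from the community. SRM is then randomised within each source: "Each set of runners will be randomly assigned to the KoR intervention group or the control group general information group in a 1:1 ratio".

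The Analytical strategy uses repeated measures to "examine differences between each intervention group(PNMC or SRM) and controls (i.e. free recreational runners), at all assessment points", for primary and secondary outcomes. A separate model for the motivational variables uses SRM vs control group as its factor. The Discussion states the hypothesis that "the sustainability of running behaviors will be higher in the SRM groups compared to the control group".

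**The concern.** Comparison (c) is given a question that it cannot answer. Both of its arms receive SRM, so no SRM effect can show in it. The arms differ in PNMC membership, which follows from where a runner was recruited.

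The design does contain a randomised answer to whether SRM adds something for runners already in the programme, namely PNMC+SRM vs PNMC. That comparison is not in the list under Study design, and the outcome analysis names free recreational runners as the controls.

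The term control group is also unstable. Study design and Analytical strategy tie it to FRR runners. Recruitment and randomization uses it for the non-SRM arm of each set. An analyst following the text could therefore estimate SRM from FRR runners alone, or could set both SRM arms against FRR controls. The first is valid but imprecise. The second mixes PNMC membership into the SRM effect.

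**Working it through.** **1. What comparison (c) estimates.** Take the mean change in FRR controls as 0. Let P be the PNMC difference without SRM, S the SRM effect in FRR runners, and I the interaction.

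| Group | Mean |
|---|---|
| FRR | 0 |
| FRR+SRM | S |
| PNMC | P |
| PNMC+SRM | P + S + I |

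- (a) PNMC − FRR = P, not randomised.
- (b) FRR+SRM − FRR = S, randomised.
- (c) PNMC+SRM − FRR+SRM = (P + S + I) − S = P + I, not randomised and without S.
- Not named: PNMC+SRM − PNMC = (P + S + I) − P = S + I, randomised. This is the added effect of SRM within the programme.

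Two illustrations: with P = 0.5, S = 0 and I = 0, (c) is 0.5 although SRM does nothing. With P = 0, S = 0.23 and I = 0, (c) is 0 although SRM works.

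**2. The plan's own sample size.** Inputs from Power calculations: d = 0.23, power 0.80, two-sided; 37 per group (alpha 0.05) or 55 (alpha 0.01); 55 per group and 220 in total after allowing for 15% dropout.

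- Two-sample formula: n = 2 × (1.960 + 0.842)² / 0.23² gives 297 per group at alpha 0.05 (442 at 0.01). The stated 37 is not reproduced.
- The only route found to both figures reads 0.23 as Cohen's f (d = 0.46) and spreads the total for one 1-df effect over four arms: (1.960 + 0.842)² / 0.23² = 148.4, and 148.4 / 4 = 37.1; at alpha 0.01, 220.8 / 4 = 55.2. It does not give the 18 per group stated for an effect of 0.50 (exact F: 34 / 4 = 8.5), so it remains a conjecture.

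The sample-size figure is a separate matter. It bears on this point only because that route would need a contrast using all four arms, and the listed pairwise comparisons do not supply one.

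**3. If SRM means FRR+SRM vs FRR only.** After 15% loss, 55 × 0.85 = 46.75, about 47 per side. With both strata, 110 × 0.85 = 93.5, about 94 per side. Outcome in SD units, SE = √(2/n), detectable d = (1.960 + 0.842) × SE, simple two-sample test at two-sided alpha 0.05:

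| | FRR only (47 vs 47) | Stratified, all four groups (94 vs 94) |
|---|---|---|
| SE | 0.206 | 0.146 |
| Power at d = 0.23 | 20% | 35% |
| Power at d = 0.46 | 61% | 88% |
| Detectable d, 80% power | 0.58 | 0.41 |

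The SE ratio is 1/√2 = 0.71, so the stratified standard error is 29% smaller and the variance is halved.

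**4. If the SRM groups are pooled against FRR controls only.** With equal arms, the SRM side averages ½S + ½(P + S + I) = S + I/2 + P/2. The SRM effect averaged over the two strata is S + I/2, so the bias is P/2. The documents give no value for P. Assumed range:

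| Assumed P (d) | Bias (d) |
|---|---|
| 0.1 | 0.05 |
| 0.3 | 0.15 |
| 0.5 | 0.25 |

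Steps 3 and 4 are alternatives. They cannot both describe one analysis.

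**5. Interaction.** I is the difference between two stratum effects, so its SE at 47 per arm is √(4/47) = 0.29, twice that of the stratified effect. Detectable I at 80% power is 2.80 × 0.29, about 0.82.

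**The case against.** The strongest reply concerns wording. Study design presents SRM vs no intervention as one of two crossed conditions, and Recruitment and randomization calls the non-SRM side of each set a control group. On that usage, the Discussion hypothesis and the model for the motivational variables could mean SRM vs no SRM across both sets, which would include PNMC+SRM vs PNMC. A journal article also need not list every contrast. This stands to the extent that one cannot say the comparison will never be made. It does not repair (c), and for the outcome analysis the article defines its controls as free recreational runners.

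Other points that stand:

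- A reader might infer that the effect of SRM on running goes untested, or is tested only with confounding. The text does not support that: (b) is a randomised test of SRM in FRR runners.
- A reader might infer that the PNMC runners are wasted. They enter (a) and (c), and (c) minus (a) equals the interaction, although no such test is described.
- Repeated measures with a baseline remove stable level differences between PNMC and FRR runners, so only a difference in change would bias the pooled reading. No single bias figure can be drawn from the documents.
- The gain in precision does not rescue the trial at d = 0.23: 35% is still low.

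The Data collection section speaks of randomisation to one of the four arms, which sits badly with recruitment by source. Even if PNMC status were randomised, S would still cancel from (c).

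**Conclusion.** The point holds, with limits. It is certain that (c) cannot show an additional effect of SRM, because this follows from the composition of the arms. It estimates the PNMC difference among SRM recipients, which is not randomised under the described recruitment. It is also clear that PNMC+SRM vs PNMC is not named, and that control group carries two meanings.

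The consequence depends on the reading. If the SRM effect comes from FRR runners only, half of the SRM-randomised information is unused, with the power and detectable effects tabulated above. If both SRM arms are set against FRR controls, the estimate is biased by half of any PNMC-FRR difference in change, whose size is unknown.

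The figures assume four arms of 55, 15% loss in each, equal variances and a simple two-sample comparison at a single time point. The planned repeated-measures model would change the absolute values.

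**What to change.** - Make the SRM effect on running behavior the comparison of SRM with no SRM in all four groups, stratified by PNMC/FRR and adjusted for baseline.
- Replace (c) with PNMC+SRM vs PNMC. Add an SRM-by-stratum interaction, labelled as having low power, and report the SRM estimate in each stratum.
- Describe any PNMC vs FRR comparison as non-randomised.
- Reword the hypothesis as SRM vs no SRM within each set of runners, and use control group in one sense throughout.

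The cost is wording in the protocol and analysis plan; no further participants or data are needed. There are two small drawbacks. The stratified effect is an average over two kinds of runner, which is why the stratum estimates should accompany it. PNMC runners also train in groups of 10–20 while being individually randomised, so they may share content and dilute the effect in that stratum.
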